### Blinding

Due to the nature of the intervention, participants, keyworkers, chief investigator and research team will be unblind to treatment allocation.

### Data collection

There will be four forms of data collection:

1Smartphone App

The smartphone app will automatically record data on app usage and engagement, including the number of prompts responded to and tests uploaded. The accuracy and reliability of uploads will be measured automatically by the application. At the end of 12 weeks post-enrolment, these data will be extracted from the software system by a researcher and entered into an SPSS database. Usage of the mCM system will be captured through an automated system and any technical problems logged. App usability will be determined using the System Usability Survey [46].

2Quantitative interviews

Outcome measures will be collected at four time points: baseline and weeks 4, 8, 12. Data will be collected for all participants unless the participant withdraws consent for continued collection of their data.

3Qualitative interviews

Semi-structured qualitative interviews (analysed thematically) with participants (n = 20) receiving the intervention will assess acceptability and perceived benefits. Interviews will be conducted following the completion of the mCM intervention. They will be audio-recorded and guided by a topic list that is applied flexibly to ensure coverage of key themes while being sensitive to emergent themes.

4Immunoassay tests

Immunoassays, which use antibodies to detect the presence of specific drugs or metabolites, are the most common method and allow for on-site instant detection of substances. Urine Drug Screen (UDS) using Access Diagnostic Tests multi-drug rapid test kit for qualitative detection of amphetamine (1000ng/ml), benzodiazepines (300ng/ml), cannabis (50ng/ml), cocaine (300ng/ml), methadone (300ng/ml), methamphetamine (1000ng/ml) and opiates (morphine; 2000ng/ml). Test cups also include a urine adulteration test strip for oxidants/specific gravity/pH adulteration test pads and a temperature test strip. Urine samples will be collected at baseline and weeks 4, 8, 12 to determine the primary outcome measure. Results will be available and recorded within 5 minutes. Oral Fluid Test (OFT) using Access Diagnostic Tests panel direct saliva oral fluid drug test kit for qualitative detection of amphetamine (50ng/ml), cannabis (12ng/ml), cocaine (20ng/ml) and opiates (40ng/ml). OFTs will be conducted remotely by participants thrice weekly as part of the CM intervention to determine heroin use. Results will be available within 5 minutes. All used equipment will be discarded immediately after use.

### Data analysis

Data analysis will be conducted by the study chief investigator ([name]). A statistical analysis plan will be developed and agreed with the trial steering committee (see below). All quantitative data will be analysed using SPSS or R. Feasibility and clinical outcomes will be summarised using appropriate statistics, e.g., mean/standard deviation or median/interquartile range for continuous variables and frequencies and percentages for categorical variables. Statistical analyses will not be powered to estimate the efficacy of the intervention (i.e., differences between arms). Estimates of treatment effects will be treated as exploratory and not used to make inferential statements. Progression to a larger confirmatory trial will be assessed based on pre-specified progression criteria (see section 3.17).

Clinical outcomes for the future confirmatory trial will also be summarised using appropriate statistics (as above). Differences between arms will be summarised (e.g., differences in means or percentages) but not used as the basis for inferential statements. The primary purpose of these estimates is to inform sample size calculations for a future confirmatory trial. This analysis is not powered to detect differences between arms. Estimates of treatment effect will be treated as exploratory and not used as the basis for inferential statements. Analyses will be done under the intention-to-treat principle: there will be no per-protocol or subgroup analyses.

All efforts will be made to avoid missing baseline data (i.e., requiring completion of baseline data before randomisation), but if this occurs, missing values will be imputed according to current recommendations. Missing scale item data will be handled as per questionnaire-specific recommendations, or if no recommendations exist, using prorating (if less than 20% of the items are missing for a given individual, the missing items will be replaced by the mean of their complete items). Given this is a feasibility study and the focus is not on between-arm comparisons, multiple imputation for missing data will not be used.

Qualitative interviews will be transcribed verbatim and subject to a thematic analysis. After familiarisation with the data, an initial coding frame will be developed, built upon from both the a priori topic guide and themes developed in the data. This coding frame will be developed and refined as data collection and analysis progress. The analytical stage will seek to discern patterns, consistencies, and divergences in the data and support the identification of themes that enable a comprehensive and detailed response to the research questions.

There are no interim analyses or audits of trial conduct planned.

### Data monitoring

A trial steering committee (TSC) will be formed before the start of recruitment consisting of an independent chair, at least two independent members and members of the research team (as non-voting members). A charter will be written and agreed upon by members outlining the remit and functioning of the TSC, including meeting frequency. The TSC will review recruitment data (and compare to pre-specified targets) and information about participant characteristics and safety (adverse events). Data will be summarised and not split by arm. Therefore, we will form an independent executive committee to monitor safety during the trial. Before each TSC meeting, the executive committee will review the number of adverse events and serious adverse events by arm and make recommendations in writing to the TSC chair (e.g., if the committee feels the trial needs to be stopped). The TSC chair would then raise these issues for discussion and decision by the TSC.

### Data protection

Researchers will collect data from the baseline and follow-up interviews on paper case report forms. These forms will be stored securely at King’s College London and entered into an SPSS database. Data stored in the trial database will include participant’s unique PIN number, initials and date of birth. The trial database will only be accessible to the chief investigator. Data will be stored in password protected KCL network. At the point of giving consent, participants will be told how their personal data is going to be used, how it will be stored, and for how long. The trial data will be registered on the King’s Data Protection Registration.

App developers protect data through advanced network segmentation, firewalls, encryption, and real-time threat monitoring. They use Amazon Shield and WAF to block cyberattacks, while AWS Network Firewall and Route 53 secure network traffic. Encryption and key management services like AWS KMS and Secret Manager safeguard sensitive information. CrowdStrike security solutions provide 24/7 threat detection, ensuring rapid response to cyber threats, ransomware, and data leaks. For authentication, Auth0 and AWS enable secure and scalable identity management, allowing seamless integration with customer identity providers. Together, these measures ensure comprehensive security across the developer’s infrastructure. Data will be retained for a period of 2 years after the completion of the research study to allow for data validation and archival purposes. During this time, the data will be anonymised, and no personal identifiers will be retained. Data will not be used for any commercial purposes.

### Adverse event monitoring

We will monitor non-serious adverse events, serious adverse events, serious adverse reactions to trial interventions, serious deterioration, and active withdrawals from treatment. Keyworkers will be asked to record (on a case report form) and notify us if they are aware of any adverse events or active withdrawals from treatment. We will contact key workers once a week to monitor possible adverse reactions. These will be recorded in a specific SPSS database, stored on a secure King’s College London drive and reported to the independent executive committee.

Keyworkers will be asked to record any adverse events. Any Serious Adverse Events should be reported to the PI within 24 hours. Any Serious Adverse Events related to the intervention will be reported to the Research Ethics Committee within 15 days.

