## Introduction

Opioid use disorder (OUD) is a major public health issue and recovery is a long-term and complex process, with the average time in treatment for opiate problems around two years longer than for other substances [1]. Deaths globally from opioid overdose continue to rise, exceeding 125,000 and accounting for approximately 25% of all drug-related deaths [2]. Half of adults receiving treatment in the UK for substance use are there for problems with opiates. Opioid Agonist Treatment (OAT) including medications such as methadone and buprenorphine, is the first-line medical intervention for OUD. These treatments are strongly supported by evidence showing their effectiveness in lowering mortality and substance use, enhancing physical and mental health, reducing criminal activity, and mitigating HIV risks and associated behaviours [3].

Despite the well evidenced effectiveness of OAT, clinical responses among sub-populations differ and concurrent heroin use among individuals in OAT is reported. In England, the rate of illicit opiate abstinence after three and six months of OAT was estimated as 46% and 48%, respectively [4]. Several risk factors are associated with continued heroin use during OAT, including suboptimal doses [3], little to no psychological therapies [5] and personal situations and environments including continued connections with drug using peer groups [6,7]. Continued heroin use is associated with high treatment drop-out rates, underscoring the need for comprehensive and innovative interventions to address this complex issue [8].

Contingency management (CM) is a behavioural intervention involving the application of positive reinforcement (e.g., monetary incentives) contingent upon evidence of positive behaviour change. CM is based on the theoretical principles of operant conditioning and is among the most efficacious psychosocial intervention in promoting substance use-related behaviours, including abstinence from smoking, alcohol and illicit drugs [9–15], medication adherence [16,17], vaccination uptake [18] and attendance [19]. CM targeting opioid abstinence in service users undergoing treatment for OUD was associated with a medium-large effect size on abstinence versus a control intervention [17].

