### Participant timeline and study visits

Participants will meet with the researcher at four time points: -t1 to complete baseline assessment, randomisation and enrolment and t1, t2 and t3 to provide bio-verified and self-reported assessment on drug use. Participants will be reimbursed £10 each time for their time. Recruitment is projected to take place between 1^st^ July 2025 and 31^st^ December 2025. See SPIRIT schedule of enrolment, interventions and assessments (Fig 1) and CONSORT diagram illustrating timeline and participant commitment (Fig 2).

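### The only adverse-event route the article describes runs through keyworkers, so events after a participant leaves treatment may go unrecorded and by-arm counts would be distorted if retention differs

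*Protocol article*

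**What the plan says.** Adverse event monitoring in the protocol article sets out the procedure in some detail: a case report form, a dedicated database, the recipients and the reporting deadlines. The source of information is the keyworker throughout. Keyworkers are to record events and "notify us if they are aware of any adverse events or active withdrawals from treatment". The team's own active step is also directed at them: "We will contact key workers once a week to monitor possible adverse reactions". The section then repeats the route: "Keyworkers will be asked to record any adverse events".

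Data monitoring states what the information is for. Before each steering committee meeting "the executive committee will review the number of adverse events and serious adverse events by arm", and it then makes written recommendations, for example "if the committee feels the trial needs to be stopped". The steering committee decides.

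The researcher has separate, direct contact with participants. Participant timeline and study visits gives the purpose of the follow-up visits as "t1, t2 and t3 to provide bio-verified and self-reported assessment on drug use". Data collection places these at weeks 4, 8 and 12 and adds: "Data will be collected for all participants unless the participant withdraws consent for continued collection of their data". Leaving treatment is not given as a reason to stop. Adverse events appear neither among the four forms of data collection nor among the measures that Outcomes lists for each assessment.

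**The concern.** A keyworker can report only what reaches the service. Knowledge of a participant's events is likely to fall once that person leaves, and a weekly prompt to the same keyworker does not restore it. The prompt is also worded for adverse reactions, which is narrower than adverse events.

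This matters in this population. The Introduction notes that "Continued heroin use is associated with high treatment drop-out rates", and continued heroin use is an entry criterion. Retention in treatment is itself listed as a clinical outcome for the future trial, so the completeness of safety data depends on something the intervention may change.

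Two consequences follow. Events after departure may be under-counted in both arms. If retention differs by arm, the comparison that the executive committee sees is distorted as well. With about 20 people per arm, one or two events can alter how such a table reads. The trial is also meant to mirror the confirmatory trial, so the weakness would carry forward.

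**Working it through.** **Step 1: set the sections side by side.**

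| Question | What the article states | Section |
|---|---|---|
| Who reports events? | Keyworkers, where aware | Adverse event monitoring |
| Is the route prompted? | Yes, weekly, through keyworkers | Adverse event monitoring |
| What happens on leaving treatment? | Active withdrawals are notified; no method is given for finding later events | Adverse event monitoring |
| Who still sees leavers? | The researcher at weeks 4, 8 and 12, unless consent to data collection is withdrawn | Participant timeline and study visits; Data collection |
| Are events asked about at those visits? | Not stated | Outcomes; Participant timeline and study visits; Data collection |
| What does the safety review use? | Numbers of events by arm | Data monitoring |

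The route described depends on contact with the service. The visits that do not depend on it are not assigned this task.

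**Step 2: size, by illustration.** The article states no event rate, retention rate or capture rate, so there is no figure of its own to reproduce. The only documented input is 40 participants randomised 1:1, taken as 20 per arm. The assumptions are:
- 0.5 events per person over 12 weeks, equal in both arms, so 20 × 0.5 = 10 true events per arm;
- leavers go half-way through on average;
- every event before leaving is captured and none afterwards.

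With retention r, the captured fraction is r + (1 − r) × 0.5.

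- 80% v 60%: 0.80 + 0.20 × 0.5 = 0.90 and 0.60 + 0.40 × 0.5 = 0.80. Recorded events are 9 v 8, ratio 0.90/0.80 = 1.125.
- 90% v 70%: 0.95 v 0.85, recorded 9.5 v 8.5, ratio 1.12.
- 90% v 50%: 0.95 v 0.75, recorded 9.5 v 7.5, ratio 1.27.
- 70% in both arms: 0.85 v 0.85, recorded 8.5 v 8.5, ratio 1.00.

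The true ratio is 1.00 in every row. The last row loses 15% of events without distorting the comparison.

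**Step 3: if risk rises after leaving.** Suppose the event rate doubles after departure, at 90% v 50% retention. True events become 10 × (0.95 + 0.05 × 2) = 10.5 and 10 × (0.75 + 0.25 × 2) = 12.5, a true ratio of 10.5/12.5 = 0.84. Recorded events stay at 9.5 v 7.5, ratio 1.27. The arm with better retention then appears worse when it is better.

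**Step 4: would a denominator alone repair this?** In the 80% v 60% case, observed time is 20 × 12 × 0.90 = 216 and 20 × 12 × 0.80 = 192 person-weeks. Rates are 9/216 = 0.042 and 8/192 = 0.042, ratio 1.00. In the Step 3 case they are 9.5/228 and 7.5/180, again both 0.042 and ratio 1.00, against a true 0.84. Follow-up time corrects for unequal observation but not for events concentrated after departure. Those have to be asked about.

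**The case against.** The strongest reply is that this is a condensed article. Protocol V1.2 and the SPIRIT schedule in Fig 1 could not be consulted, and an adverse-event item at weeks 4, 8 and 12 could be listed in either. Nothing in the text forbids a researcher from recording an event learned at a visit. This stands to the extent that a reader may not infer that participants are never asked. The text supports only that the keyworker is the sole route described. It is still a fair point, because the section fixes the procedure in detail and names no other source.

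A reader might also infer that events in leavers are simply missed, or that capture is haphazard. The documents do not support that: keyworkers are prompted weekly, active withdrawals are notified, and keyworkers may hear of some later events.

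A third tempting inference is a recorded ratio of 0.80/0.60 = 1.33, with 20% to 40% of participants contributing no observable events. That requires every leaver to go on day 0. Events before departure are observable, and half-way departure gives 1.125.

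Finally, no numerical threshold or test is attached to the by-arm review, an independent committee applies judgement, and the trial is not powered for between-arm differences. That limits the consequence, and a one-event shift would not by itself trigger a decision. It does not remove the benefit of more complete data for that judgement.

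**Conclusion.** The point holds in a limited form. As described, adverse-event capture depends on contact with the treatment service, while researcher visits that do not depend on it go unused for this purpose. Under-recording after departure is possible in both arms. A distorted comparison needs a further condition, that retention differs by arm, and the article gives no evidence either way: its remark on drop-out concerns the population, not a difference between arms.

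On the stated assumptions the shift is about one event per arm comparison at 80% v 60% retention and two at 90% v 50%. It is zero when retention is equal. No sample-size or precision figure in the article is affected. The change is worth making because it is cheap and because the by-arm numbers may support a recommendation to stop.

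**What to change.** Keep the keyworker route and add to it:

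1. At the existing week 4, 8 and 12 interviews, ask every randomised participant in both arms, whether or not still in treatment, a standard adverse-event question that covers hospital contact and overdose.
2. Record the source of each event (participant or keyworker), so that double reports can be merged and the yield of each route seen.
3. Give the executive committee the observed follow-up time per arm with the counts.

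If the full protocol or Fig 1 already provides for the first item, one sentence in Adverse event monitoring settles it.

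The cost is one form page and a few minutes per visit, with no extra visits. More non-serious events will be recorded. Some dependence remains, because capture from participants would be limited by visit attendance, and Table 1 counts 70% attendance at the 12-week interview as Green.

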### End of study

The end of the study refers to the point at which trial databases are locked for analysis.

### Progression criteria

Progression to a larger confirmatory trial will be evaluated based on the pre-specified progression criteria (see Table 1). However, not achieving ‘Green’ does not necessarily indicate the unfeasibility of a future trial but would indicate that changes are needed to recruitment procedures, attendance record keeping and follow-up resources.

**Table 1 pone.0324516.t001:** Pre-specified progression criteria.

	Green	Amber	Red
Number of eligible patients enrolled over the 6-month recruitment period	≥30, at least 15 per arm	≥20, at least 10/arm	<20
Percentage of screened patients who are eligible for inclusion in the feasibility trial.	≥50%;	≥30%;	<30%
Adherence to the intervention based on percentage of requested videos uploaded	≥70% in CM arm	≥50% in CM arm	<50% in CM arm
Percentage of urine drug screenings completed, overall	≥70% in all arms	≥50% in all arms	<50% in all arms
Number and percentage attending follow-up interview at end of 12-week intervention period (compared to number randomised)	≥70%	≥50%	<50%

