### Sample size

One of the aims of this feasibility trial is to estimate the parameters needed to inform a sample size calculation for the future confirmatory trial. A sample of 40 was chosen based on the resources available and the number required to estimate feasibility parameters with adequate precision. With 40 participants, we will be able to estimate the expected recruitment rate of 6.7 patients per month (primary feasibility outcome) to within a 95% confidence interval of 4.3 (4.8 to 9.1 patients recruited/month). For the second feasibility outcome (‘Percentage of screened patients eligible for inclusion and reasons for ineligibility’), we will be able to estimate the expected percentage of 50% to within a 95% confidence interval of 42% to 58%. This is based on screening 160 patients, of whom we expect 50% to be eligible, and of these, a half are expected to consent to participate.

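### Two rows of Table 1, urine screening and enrolment, leave some results with no Green, Amber or Red category

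*Protocol article*

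**What the plan says.** The Data analysis and Progression criteria sections of the Protocol article both refer the decision on a larger trial to Table 1.

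- **Enrolment row.** Green is "≥30, at least 15 per arm" and Amber is "≥20, at least 10/arm". Red is a total below 20, with no condition on the arms.
- **Urine row.** The label is "Percentage of urine drug screenings completed, overall". The cells read "≥70% in all arms" for Green, "≥50% in all arms" for Amber and "<50% in all arms" for Red.
- **Follow-up row.** Week-12 attendance is taken as a share of the number randomised, with cuts at 70% and 50% and no condition on the arms.

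The text beside the table adds that missing Green need not mean a trial is unfeasible, but signals that procedures need changing. It gives no rule for a result that falls outside all three bands. The Randomisation section specifies simple 1:1 allocation without stratification or minimisation.

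**The concern.** A traffic-light table is useful only if every result it may meet has one colour fixed in advance. In the urine and enrolment rows, Red is not the complement of Amber. A result can therefore fail Amber without being Red, and its reading would have to be settled after the data are known.

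The urine row matters more. It measures completion of the samples that supply the proposed primary clinical outcome of the confirmatory trial. Its label and its cells can also be read as two different rules, one pooled and one by arm. The gaps lie close to the Amber/Red boundary, which is where a pre-specified rule is most needed.

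**Working it through.** **Inputs from the Protocol article.** The planned size is 40, since 160 screened × 0.5 eligible × 0.5 consenting = 40, and 40/6 = 6.7 per month, as the Sample size section states. Allocation is simple and 1:1. Post-randomisation urine samples fall at weeks 4, 8 and 12, so 20 participants per arm give 20 × 3 = 60 samples per arm. The document gives no expected completion rates by arm, so those used below are assumptions.

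**Urine row, logic.** Let A and B be the completion percentages in the two arms.

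- Green: A ≥ 70 and B ≥ 70.
- Amber: A ≥ 50 and B ≥ 50 (and not Green).
- Red: A < 50 and B < 50.
- Left over: one of A, B at or above 50 and the other below.

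This step needs no assumption.

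| Arm 1 | Arm 2 | Pooled | Pooled reading | By-arm reading |
|---|---|---|---|---|
| 51/60 = 85% | 27/60 = 45% | 78/120 = 65% | Amber | none |
| 57/60 = 95% | 29/60 = 48.3% | 86/120 = 71.7% | Green | none |

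**Urine row, size.** Let q be the probability that an arm's observed completion is below 50%. Then P(no category) = q₁(1 − q₂) + q₂(1 − q₁). Each person's completed samples out of 3 are modelled as beta-binomial with mean p and within-person correlation 0.5 (assumed), with 20 people per arm. This gives q = 0.009 at p = 70%, 0.115 at 60% and 0.464 at 50%.

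- 70%/50%: 0.009 × 0.536 + 0.464 × 0.991 = 0.46
- 50%/50%: 2 × 0.464 × 0.536 = 0.50
- 60%/60%: 2 × 0.115 × 0.885 = 0.20
- 70%/70%: 2 × 0.009 × 0.991 = 0.02

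Varying the correlation from 0.3 to 0.7 leaves the first figure at 0.46 to 0.47 and the second at 0.50. The last stays at or below 0.03.

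**Enrolment row.** A total n ≥ 20 with an arm below 10 is neither Amber nor Red. Under simple randomisation the size X of one arm is binomial(n, 0.5), so P(no category) = 1 − P(10 ≤ X ≤ n − 10).

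| n | P(both arms ≥ 10) | P(no category) |
|---|---|---|
| 20 | 184,756/1,048,576 = 0.176 | 0.82 |
| 24 | 0.692 | 0.31 |
| 30 | 0.957 | 0.04 |
| 40 | 0.9993 | 0.0007 |

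The per-arm minimum bears on Green too. At exactly 30 recruits both arms must have 15, which has probability 0.14; at 40 recruits the probability of at least 15 in each arm is 0.92.

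**Other rows.** The eligibility, adherence and follow-up rows each compare a single percentage with two cuts and have no gap. Green also satisfying the Amber condition is the usual cumulative reading and is not a fault.

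**The case against.** **The sizes depend on where one looks.** This stands. The large urine figures need an arm with true completion near 50%; at 70%/70% the gap is about 0.02. The enrolment gap is negligible at the planned 40 and matters mainly for recruitment in the low to mid 20s.

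***Overall* may mean across all scheduled samples, then judged by arm.** That is a fair reading and removes the conflict with the cells. It does not close the gap, and the label does not say it.

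**An unclassified result is at least not Green, and the text says what that implies.** This is true, but the caveat does not separate Amber from Red. The statistical analysis plan is not shown; even so, Table 1 is presented as the pre-specified rule, and its cells as worded leave the gap.

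**Two stronger readings are tempting.**

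- A reader might infer that mixed-arm results are the expected case because only the mCM arm earns incentives. The documents do not support this. The Intervention section ties those payments to heroin-negative saliva tests, and the Participant timeline section reimburses £10 per researcher visit without distinguishing arms. A difference between arms is plausible in an open-label trial, but no more than that.
- A reader might infer that the follow-up row is also defective because pooling can hide a poor arm: 18/20 and 10/20 is 28/40 = 70%, which is Green. But 10/20 is 50%, not below it. Green with an arm under 50% needs a split such as 20/20 and 8/20, with probability 0.08 at assumed true rates of 90%/50% and 0.0002 at 70%/70%. The row is exhaustive and pooling is a legitimate design choice.

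**Conclusion.** The point holds for two rows. That the urine and enrolment rows are not exhaustive follows from the wording of Table 1 alone. The urine label adds an ambiguity that can change the result from no category to Green.

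The probabilities rest on assumptions: 20 participants per arm with three samples each, the illustrative completion rates, and allocation that is truly simple. Blocked allocation would shrink the enrolment gap. The defect is confined to results near the 50% cut for urine and to recruitment well short of 40. It is nonetheless a failure of a stated decision rule at its own boundary, and it is cheap to correct. It does not show that progression is likely to be misjudged, and it does not extend to the follow-up row.

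**What to change.** Before any arm-level data are seen, reword two Red cells so that Red is whatever fails Amber.

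- **Urine row:** Red if either arm is below 50%. Delete *overall* from the label, or state that it means across all scheduled samples within each arm.
- **Enrolment row:** Red if the total is below 20 or either arm has fewer than 10. Alternatively, base all three bands on the total only, which keeps chance imbalance between arms from deciding a recruitment criterion.

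**Cost.** This is a wording change, although the Methods section requires sponsor and ethics committee agreement for amendments. Some results now unclassified become Red. At assumed urine completion of 50%/50%, P(Red) rises from 0.464² = 0.22 to 1 − 0.536² = 0.71. In the enrolment row, keeping the arm condition would make 82% of trials with exactly 20 recruits Red, which favours the total-only option.

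No change is required in the follow-up row; reporting week-12 attendance by arm beside the pooled figure would be enough. Making that row per-arm would not be a small step: with 20 per arm and true attendance of 70% in both, P(Green) would fall from 0.58 to 0.37.
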